#### Exclusion criteria

2.4.2

DM images fulfilling any of the following criteria will not be collected.

1.Tomosynthesis and synthetic 2D mammographic images2.Spot compression views3.Poor image quality4.Inappropriate images as judged by the local investigators

### Construction of an AI algorithm

2.5

The machine learning community has been applying deep learning in various medical imaging fields, including mammography images. Based on this work, we have developed a convolutional neural network. The neural network includes pairs of the convolutional layer and the pooling layer with the fully convolutional layers. The classification output is calculated by the softmax function.

From mammography images, corresponding masking images of breast lesions will be created manually, indicating the area of the lesions. Mammography images will then be cropped with rectangular patches so that the lesions are included in these patches, and patches will be classified as benign or malignant. Patches in which neither benign nor malignant tumors are included will also be cropped from the mammography images.

These patches will be randomly divided into the training dataset, the validation dataset, or the test dataset. The neural network will be fine-tuned to classify whether these patches contain either a benign or a malignant tumor, or neither of them.

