### Endpoints

2.3

The primary endpoint is the sensitivity and specificity of the AI system to detect breast cancer with the test image set. Sensitivity is calculated as the number of images in which the AI system correctly diagnoses cancer among all images with biopsy-proven cancer. Specificity is calculated as the number of images in which the AI system correctly diagnoses normal or benign lesions among all images without cancer.

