## Discussion

3

AI with deep learning needs good training data to work properly. Thus, we put a premium on the quality of training image data in the development of our AI. Experienced and qualified readers will interpret mammograms and define the outline of the malignant or benign lesions. To delineate the outline precisely, surgical pathology reports or the results of other imaging modalities will be taken into account whenever possible. The diagnosis will be confirmed by histopathology. Benign diseases without available pathological results will be clinically diagnosed after at least 2 years of follow-up. To avoid biased collection toward a particular lesion, a target number of images has been set according to each radiographic finding in breast cancer or in each benign disease.

Mammographic images will be obtained from multiple participating centers. The DM images will be acquired with devices from various vendors. The images used in this study will be taken from women aged 20 or older (not confined to the recommended screening age), and originating not only from screening but also from clinical practice. Larger and more advanced breast cancers are expected from clinical practice, with different characteristics from screen-detected cancers. These various kinds of data will increase the generalizability of our AI algorithms. Alongside images, we will collect clinicopathological features of each case, including pathological diagnosis, tumor diameter, hormone receptor status, HER2 status, breast density, and vendors. This will enable us to perform detailed analysis of which patient population is more suitable for AI reading.

Our study has a limitation. The dataset will come only from Japanese women. Thus, our AI system might not be applicable to Caucasian patients. However, it will probably work well in Asian women who have similar breast density, size, and shape to Japanese women.

Japan has a double reading system in screening mammography. When the ability of AI reading is shown to be on a par with that of human reading, images of normal breasts or benign lesions that do not have to be read by a human can be selected by AI beforehand (the first reader role). This AI preselection might obviate the need for double reading. However, future studies will be required to clarify how much the workload of readers is reduced or which threshold of cancer probability for alerting humans is optimal.

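### Sensitivity and specificity are defined per image, but the only test dataset described consists of patches cropped around lesions already outlined; the two need reconciling, with a whole-image test.

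*Protocol article*

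**What the plan says.** The endpoint is an image count. Section 2.3 states: "The primary endpoint is the sensitivity and specificity of the AI system to detect breast cancer with the test image set". It continues: "Sensitivity is calculated as the number of images in which the AI system correctly diagnoses cancer among all images with biopsy-proven cancer", and "Specificity is calculated as the number of images in which the AI system correctly diagnoses normal or benign lesions among all images without cancer".

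Section 2.5 works with patches. Lesion masks are drawn by hand: "corresponding masking images of breast lesions will be created manually, indicating the area of the lesions". The images are then cut to fit: "Mammography images will then be cropped with rectangular patches so that the lesions are included in these patches". Background is added: "Patches in which neither benign nor malignant tumors are included will also be cropped from the mammography images". The split is made on these pieces: "These patches will be randomly divided into the training dataset, the validation dataset, or the test dataset". The network's task is to label each patch as benign, malignant or neither.

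The Discussion (section 3) says that qualified readers draw the outlines and adds: "To delineate the outline precisely, surgical pathology reports or the results of other imaging modalities will be taken into account whenever possible". Section 2.1 gives the aim as detecting cancer on mammograms with high specificity. Section 2.6 sets targets of at least 80% for both measures, citing reader sensitivity and specificity of about 85% and 90% and a mammography sensitivity of 77% from a Japanese trial.

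**The concern.** The two sections name different units for the same evaluation. An endpoint defined over images cannot be read off a test dataset of patches unless some rule links them, and the article gives none.

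The difference is more than bookkeeping. A patch that contains a masked lesion has been placed by someone who already knew where the lesion was. A cancer that the system would overlook when searching a whole breast cannot count as a miss on such a patch. For specificity, a patch denominator is set by how many background pieces are cut, and section 2.5 gives neither a number nor a selection rule. The reader figures behind the 80% target come from people reading mammograms. Patch accuracy is a different quantity, so meeting 80% on patches would not show that the target had been met.

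**Working it through.** **Units side by side.** Section 2.3: numerators and denominators are images. Section 2.5: the items in the test dataset are patches. Section 2.6: the benchmarks are for reading mammograms. No section describes inference on a complete image or an aggregation rule.

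**The plan's own figures.** 5000 cancer + 10,000 benign = 15,000 images, as stated. With at least 1000 normal images the total is 16,000, of which 10,000 + 1000 = 11,000 are without cancer. The total rests on earlier study designs, so there is no power calculation to reproduce, and this point does not depend on one.

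**Illustration of specificity.** Let sB be specificity on benign-lesion patches, s0 specificity on background patches, and k the number of background patches per image. The documents give none of these, so all are assumptions. One lesion patch per benign image is also assumed, with background patches cut from all 16,000 images and all collected images used, since the split proportions are not given.

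- Per patch: (10,000·sB + 16,000·k·s0) / (10,000 + 16,000·k)
- Per image, if any positive patch makes the image positive and patches are independent: (10,000·sB·s0^k + 1000·s0^k) / 11,000, for k ≥ 1

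With sB = 70% and s0 = 98%, at k = 1: per patch (7000 + 15,680) / 26,000 = 87.2%; per image (8000 / 11,000) × 0.98 = 71.3%.

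| k | Per patch | Per image |
|---|---|---|
| 0 | 70.0% | – |
| 0.5 | 82.4% | – |
| 1 | 87.2% | 71.3% |
| 2 | 91.3% | 69.8% |
| 5 | 94.9% | 65.7% |
| 10 | 96.4% | 59.4% |

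**Range.** Per-patch specificity reaches 80% when k = 10,000·(0.80 − sB) / [16,000·(s0 − 0.80)]. For sB from 60% to 75% and s0 from 95% to 99%, k is between 0.16 (sB 75%, s0 99%) and 0.83 (sB 60%, s0 95%), which is less than one background patch per image. Over the same range the per-image figure is at most 8500 × 0.99 / 11,000 = 76.5%, at k = 1. That shortfall is partly built in: with sB = 75% and perfect background patches the ceiling is 8500 / 11,000 = 77.3%. If sB were already 80% or more, background patches would not be needed to reach the target.

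**Sensitivity.** Sensitivity on malignant patches does not depend on k. Its gap from whole-image sensitivity depends on how often the system fails to find the lesion, for which the article offers no figure, so no number is given here.

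**The case against.** The strongest reply is that no sentence says the primary endpoint is computed on patches. Section 2.3 speaks of a test image set. Section 2.5 is about building the algorithm, and its patch test dataset could be a development hold-out. Training on patches and then running on whole images would fit both sections, and the full protocol may say so. Under section 2.3 as written, background patches cannot enter the specificity denominator at all. This stands as a limit: the consequences described here are conditional on the endpoint being computed on the patch dataset. It does not remove the inconsistency, because section 2.5 expressly assigns patches to the test dataset and the article describes no other.

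Several stronger readings are tempting but not supported:

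- A reader might infer that the study certainly does not measure detection. The class for neither lesion type does test lesion against background within patches; what is not described is a search of the whole breast.
- A reader might infer that every outline was drawn from pathology. The Discussion says pathology or other imaging where possible, and section 2.4.1 accepts benign lesions confirmed by follow-up or imaging.
- A reader might assume that background patches are easy negatives. The article says nothing about their difficulty.
- A reader might take 0.98^k as the specificity to expect (82%, 67% and 36% for 10, 20 and 50 patches). That formula applies only to images without a lesion and needs independent patches, which is doubtful within one breast.

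**Conclusion.** The inconsistency is in the text: images in section 2.3, patches in section 2.5, and nothing joining them. If section 2.5 is followed as written, the result is patch accuracy, which cannot count localisation failures and cannot be set against the 80% target. Under the assumed inputs, the choice of unit and of k moves specificity across 80% with the network unchanged, and in opposite directions: more background patches raise it per patch and lower it per image under the any-positive rule. The percentages rest on assumed performance, patch independence and that rule, so they show that the effect can matter and do not estimate it for this system. The documents do not establish that the sponsor will compute the endpoint on patches. They do leave the primary endpoint without a test dataset on which it can be computed as defined.

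**What to change.** - Assign women, with all their images, to training, validation and test before any cropping. The random division of patches in section 2.5 can put pieces of one mammogram in both training and test, which would leave no clean whole-image test set.
- Use patches for training and development only.
- Run the locked network on the complete test mammograms without masks.
- Prespecify one rule that turns outputs into an image call (the maximum malignant probability is one option among several) and one cut-off chosen on the validation set.
- Compute the section 2.3 endpoints from those image calls, and report patch accuracy as a development metric only.

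If the full protocol already does this, section 2.5 only needs wording that says so. Otherwise the cost is a protocol change and some computing time, since whole images are already being collected. The figures will probably be less favourable than patch accuracy, but they can be compared with the target.

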#### Inclusion criteria

2.4.1

DM images fulfilling all the following criteria will be collected.

1.Taken after 20102.Images meeting either one of the following criteriaVisible breast cancer or benign lesions on images.Normal breast.3.If cancer or benign lesions are visible on images, their outlines can be traced manually.4.Images from patients aged 20 or older.5.Available mediolateral oblique view with or without cranial-caudal view.6.No visible axillary lymph node metastasis from breast cancer.7.Images from patients with no previous history of chemotherapy, endocrine therapy or radiotherapy.8.Images from patients who have not received any previous surgical breast procedure including partial resection, breast reconstruction, incisional biopsy, vacuum-assisted biopsy, and mammoplasty9.Read by readers ranked A according to the Japan Central Organization on Quality Assurance of Breast Cancer Screening.10.Benign lesions, breast cancer, and normal breast on images are confirmed by the following criteria.<Benign lesions>Meeting one of the following criteriaConfirmed by histopathology.Without malignancy development over at least 2 years of follow-up.Findings clearly indicating a simple cyst by mammography and other imaging modalities.<Breast cancer>Confirmed by histopathology.<Normal breast>Meeting either one of the following criteriaIn addition to the findings of mammography, ultrasonography and MRI do not detect any lesions.Without malignancy development over at least 2 years of follow-up when no other imaging modalities except mammography are performed.

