### Statistical analysis

2.6

The Breast Cancer Surveillance Consortium reported readers’ interpretive performance with sensitivity and specificity of around 85% and 90% respectively.^[24]^ The sensitivity of mammography was 77% in the J-SATRT trial conducted in Japan.^[25]^ Thus, we set the target sensitivity and specificity at 80% or more with the AI system. By referring to the design of previous studies.^[26]^ 15,000 DM images will be collected in this study. They will consist of 5000 images with breast cancer and 10,000 images with benign lesions. At least 1000 images of normal breasts will also be collected for use as reference data.

We will categorize images with breast cancer according to the main findings (mass, focal asymmetric density, calcification, architectural distortion). At least 750 images will be collected in each category.

There will be a limit on the number of accumulated images with each benign lesion. Simple cyst 1500; fibroadenoma or benign phyllodes tumor 1500; intraductal (intracystic) papilloma 1500; adenoma 100; adenomyoepithelioma 100; sclerosing adenosis 1000; mastopathy 1000; breast calcifications 4000; other benign disease 300 images.

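### The random split into training, validation and test sets is made on cropped patches with no grouping by woman, so the primary sensitivity and specificity are expected to be optimistic by an unknown amount

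*Protocol article*

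**What the plan says.** Section 2.5 of the protocol article sets out a sequence. Lesions are masked by hand, and then "Mammography images will then be cropped with rectangular patches so that the lesions are included in these patches". Lesion-free crops are added: "Patches in which neither benign nor malignant tumors are included will also be cropped from the mammography images". Only after that does the split take place: "These patches will be randomly divided into the training dataset, the validation dataset, or the test dataset". The network learns to label each patch as benign, malignant or neither.

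Section 2.4.1 (Inclusion criteria) asks for "Available mediolateral oblique view with or without cranial-caudal view", so a woman may contribute one or two views of the same breast. No limit of one image per woman is given.

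Section 2.3 (Endpoints) reads: "The primary endpoint is the sensitivity and specificity of the AI system to detect breast cancer with the test image set". It counts in images: "Sensitivity is calculated as the number of images in which the AI system correctly diagnoses cancer among all images with biopsy-proven cancer". Section 2.6 (Statistical analysis) states that "we set the target sensitivity and specificity at 80% or more with the AI system", and sizes the collection in images: "They will consist of 5000 images with breast cancer and 10,000 images with benign lesions".

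The article describes no other test set, whether external or held out by woman or institution. The only limitation it acknowledges (section 3, Discussion) is that the data come from Japanese women alone.

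**The concern.** A test set should show how the system performs in women it has not met. When patches are the unit divided, the crops of one woman are not kept together. The network may be tested on tissue from a breast it was trained on, or on the same lesion seen in the other view. Success on such patches is partly recognition, so it says less about a new woman.

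This touches the only stated primary endpoint and its 80% target. A system that falls short in unseen women could appear to pass. The validation set comes from the same split, so it would understate overfitting during tuning. The Discussion foresees the AI setting aside images that no human need read once parity with human reading is shown, so an optimistic estimate would have consequences.

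There is also a mismatch of units. Section 2.3 needs a set of test images, section 2.5 produces a set of test patches, and one image may have patches in more than one set.

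**Working it through.** **Inputs from the document.** The unit divided is the patch, and lesion and lesion-free patches are both cropped (2.5). The second view is optional (2.4.1). The endpoint is counted per image (2.3). The target is 80%, and the collection is 5000 + 10,000 = 15,000 images, not women (2.6). The article gives no split ratio, number of patches per woman or share of women with both views. These are assumptions below.

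**Step 1: any patch of the same woman.** Let t be the training share and s the number of other patches from the same woman. With patches allocated independently, the probability that a test patch has at least one same-woman patch in training is 1 − (1 − t)^s.

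| t | s = 1 | s = 3 (two views, two patches each) |
|---|---|---|
| 0.6 | 1 − 0.4 = 0.60 | 1 − 0.4³ = 0.936 |
| 0.7 | 1 − 0.3 = 0.70 | 1 − 0.3³ = 0.973 |
| 0.8 | 1 − 0.2 = 0.80 | 1 − 0.2³ = 0.992 |

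**Step 2: lesion patches only, one per image.** Let q be the share of women with both views. Two-view women supply 2q/(1 + q) of the images, and each such image has one sibling. The affected share of test patches is t × 2q/(1 + q).

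| q | t = 0.6 | t = 0.8 |
|---|---|---|
| 0.25 | 0.6 × 0.400 = 0.24 | 0.8 × 0.400 = 0.32 |
| 0.50 | 0.6 × 0.667 = 0.40 | 0.8 × 0.667 = 0.53 |
| 1.00 | 0.6 × 1 = 0.60 | 0.8 × 1 = 0.80 |

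A simulation with 5000 cancer images gave matching values (0.24, 0.40 and 0.60; 0.32, 0.53 and about 0.80). The share is zero only if each woman contributes exactly one patch, which the article does not require.

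**Step 3: what this could do to the target (illustration only).** Assume a true sensitivity of 75% in unseen women and 90% on test patches with a helpful sibling in training. With affected share p, apparent sensitivity is 0.75(1 − p) + 0.90p:
- p = 0.3: 0.525 + 0.270 = 79.5%
- p = 0.6: 0.300 + 0.540 = 84%
- p = 0.8: 0.150 + 0.720 = 87%

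The 80% line is crossed at p = (0.80 − 0.75)/0.15 = 1/3. The 75% and 90% are not in the document. They show only that overlap of this order can move a result across the target.

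**Step 4: after a split by woman.** The share of test patches with a same-woman patch in training is 0% by construction, whatever the ratio.

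**The case against.** The strongest defence is that this is a condensed article. Section 2.5 gives no ratio, patch size or patch count, and a fuller protocol could keep each woman's patches together. That limits certainty about what will be done in practice. It does not rescue the text, which names a unit, and that unit is the patch.

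Several stronger readings are tempting, and the document does not support them:

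- *Nearly the whole test set is contaminated.* This needs three siblings per patch, that is, both views for every woman and a lesion-free crop from each image. The second view is optional, and the article does not say that every lesion image yields a lesion-free crop.
- *Sensitivity and specificity are inflated, as a fact.* Siblings differ in effect. A lesion-free patch carries a different label from a cancer patch of the same woman, and remembering her tissue as lesion-free could even push the cancer patch towards a miss. Clear upward pressure on sensitivity comes from the same lesion in another view or a repeated crop, which the plan permits but does not require. Upward bias is the expected direction, not a derived result.
- *No test image set exists.* The article does not say whether the test images of section 2.3 and the test patches of section 2.5 are the same data. What can be said is that the units differ.
- *Overfitting would go unseen.* Some validation patches may have no sibling in training, so it would be understated rather than hidden.

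These points limit the size and certainty of the claim. The central point stands.

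**Conclusion.** The point holds as a badly fixed rule, not as an omission. As written, the split allows patches of one woman into both training and test, and patches of one lesion where both views or repeated crops are used. The primary sensitivity and specificity are therefore expected to be optimistic against the 80% target.

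The extent of overlap rests on assumed training shares of 60-80%, independent allocation of patches, and the assumed sibling counts and two-view shares shown above. The size of the bias itself cannot be derived from the document. Separately, and whatever that size, sections 2.3 and 2.5 must be reconciled on whether the test unit is the image or the patch. Because the flaw bears on the validity of the sole stated endpoint, it should be corrected before the split is made.

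**What to change.** Replace the sentence on the split in section 2.5 with:

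> Women will be randomly allocated to training, validation or test before any patch is cropped, stratified by cancer/benign/normal. All images, views, both breasts and all patches of a woman stay in one set. Test women are not used for training, tuning or threshold choice. Sensitivity and specificity are computed per image on the test women's images.

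The last sentence brings sections 2.3 and 2.5 to one unit.

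The cost is this change of wording and a patient identifier carried through the split code. No extra images are needed. The downside is that reported performance will probably be lower.

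This removes same-woman leakage only. Signatures of site or device would still be shared between training and test, and stratifying the split by institution would not remove them. That would require holding out whole institutions for the test set.

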### Statistical analysis

2.6

The Breast Cancer Surveillance Consortium reported readers’ interpretive performance with sensitivity and specificity of around 85% and 90% respectively.^[24]^ The sensitivity of mammography was 77% in the J-SATRT trial conducted in Japan.^[25]^ Thus, we set the target sensitivity and specificity at 80% or more with the AI system. By referring to the design of previous studies.^[26]^ 15,000 DM images will be collected in this study. They will consist of 5000 images with breast cancer and 10,000 images with benign lesions. At least 1000 images of normal breasts will also be collected for use as reference data.

We will categorize images with breast cancer according to the main findings (mass, focal asymmetric density, calcification, architectural distortion). At least 750 images will be collected in each category.

There will be a limit on the number of accumulated images with each benign lesion. Simple cyst 1500; fibroadenoma or benign phyllodes tumor 1500; intraductal (intracystic) papilloma 1500; adenoma 100; adenomyoepithelioma 100; sclerosing adenosis 1000; mastopathy 1000; breast calcifications 4000; other benign disease 300 images.

